## Abstract

*Background*: ST-T segment elevation myocardial infarction (STEMI) is a critical condition that requires rapid diagnosis and treatment. Recently, various ECG recording devices have been developed. In this study, we aim to determine the utility of a 6-lead handheld ECG recording device to shorten the time taken for the diagnosis of inferior wall STEMI. *Methods and Design*: HINT-MI is an investigator-derived, observational, prospective study that will evaluate the ability of a handheld 6-lead ECG device to diagnose acute inferior wall STEMI. Patients who have undergone coronary angiography for STEMI or for other reasons will be enrolled in the study. This study aims to evaluate sensitivity and specificity of a handheld 6-lead ECG device by the level of agreement with a standard 12-lead ECG for diagnosing inferior wall STEMI. Further, we will determine whether the use of the handheld device can reduce the time needed for reperfusion treatment through faster diagnosis. *Conclusions*: This study aims to investigate the feasibility of a handheld 6-lead ECG device for diagnosing inferior wall STEMI to reduce the time required to diagnose inferior wall STEMI and to allow timely treatment.

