This study aims to evaluate the level of agreement between the results of a handheld 6-lead ECG device and a standard 12-lead ECG in the diagnosis of inferior wall STEMI to determine whether the use of the handheld device can reduce the time needed for reperfusion treatment through faster diagnosis.

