## 2. Materials and Methods

### 2.1. Study Design

Handheld 6-lead ECG device for the early detection of acute inferior wall ST-T segment elevation myocardial infarction (HINT-MI) is an investigator-derived, multicenter, observational prospective study to evaluate the ability of a handheld 6-lead ECG device to diagnose acute inferior wall STEMI (reg. no. clinicaltrials.gov NCT05777083). By comparing a 6-lead ECG using a handheld device and a 12-lead standard ECG in patients with various types of STEMI and those without STEMI, the diagnostic accuracy of the 6-lead handheld ECG device in inferior wall STEMI will be evaluated.

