### 2.2. Primary Objectives

This study will investigate the sensitivity and specificity of a handheld six-lead ECG device compared to a 12-lead ECG for the diagnosis of acute inferior wall myocardial infarction.

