### 2.3. Study Population

Two primary PCI centers in South Korea are participating in this study, representing full coverage of all levels of care, including state-of-the-art tests, monitoring, imaging equipment, the latest treatment regimens, access to specialists, and intensive care units. The study subjects will consist of two types of patients: (a) patients who will first visit the emergency room and be diagnosed with various types of STEMI by a 12-lead ECG and undergo primary PCI, and (b) patients without STEMI who will undergo coronary angiography for chest pain after visiting an outpatient clinic. All the patients enrolled in this study will provide their voluntary informed consent.

In the case of patients with all kinds of STEMI, a surface 12-lead ECG in the emergency room and coronary angiography results will be used to screen for STEMI. Patients initially diagnosed with STEMI by ECG but later confirmed not to have a myocardial infarction by additional tests (coronary angiography and serum cardiac markers) will be excluded from the study. The diagnosis of myocardial infarction will follow the criteria of the fourth universal definition of myocardial infarction [4]. Patients with severe complications of myocardial infarction such as cardiogenic shock, respiratory failure, or decreased consciousness will be also excluded.

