### 2.5. ECG Recording

#### 2.5.1. Patients with STEMI

Among all patients with various types of STEMI who visit the emergency room and do not meet the exclusion criteria, an ECG using a 6-lead handheld device will be recorded, in addition to a basic 6-lead ECG monitor and a 12-lead ECG. In general, all patients with STEMI who visit the emergency room undergo a 12-lead ECG in the emergency room and then move to a catheterization laboratory for coronary angiography. In this study, the first 6-lead ECG by the handheld device will be recorded for 30 s in the supine position. To prevent any treatment delays, we will record the handheld ECG as part of the procedure preparation process, including the attachment of basic monitoring. If the first handheld recording is not available, it will be recorded before leaving the catheter lab.

During the procedure, a wired 6-lead ECG is typically attached to continuously monitor the patient’s condition. We will record this data for 30 s before and after the procedure. Finally, a 12-lead ECG will be recorded within 1 h after moving to the intensive care unit or emergency room, according to the general myocardial infarction treatment plan.

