## 4. Conclusions

If a handheld 6-lead ECG device is capable of diagnosing inferior wall STEMI, it can reduce the time required to diagnose inferior wall STEMI and enable early treatment.

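### The stated aim of showing a shorter time to reperfusion cannot be answered, because every STEMI patient has been diagnosed by 12-lead ECG before the handheld is recorded

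*Protocol article*

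**What the plan says.** The time aim appears in three places in the protocol article.

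- **Abstract, Background:** the study is introduced as establishing how useful the handheld is for shortening time to diagnosis of inferior wall STEMI.
- **Abstract, Methods and Design:** after the accuracy aim, and joined to it by the word further, comes "we will determine whether the use of the handheld device can reduce the time needed for reperfusion treatment through faster diagnosis".
- **Introduction, last paragraph:** agreement with the 12-lead ECG is to be evaluated "to determine whether the use of the handheld device can reduce the time needed for reperfusion treatment through faster diagnosis".

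Section 4 closes by saying that, if the device can diagnose inferior wall STEMI, "it can reduce the time required to diagnose inferior wall STEMI and enable early treatment".

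The methods describe a different study. Section 2.1 calls it a "multicenter, observational prospective study to evaluate the ability of a handheld 6-lead ECG device to diagnose acute inferior wall STEMI". Section 2.2 gives the sole primary objective: "This study will investigate the sensitivity and specificity of a handheld six-lead ECG device compared to a 12-lead ECG". Section 2.3 defines the STEMI group as "patients who will first visit the emergency room and be diagnosed with various types of STEMI by a 12-lead ECG and undergo primary PCI", and adds that "a surface 12-lead ECG in the emergency room and coronary angiography results will be used to screen for STEMI". Section 2.5.1 says that STEMI patients generally "undergo a 12-lead ECG in the emergency room and then move to a catheterization laboratory for coronary angiography". It places the handheld recording within procedure preparation, with a fallback of any time before the patient leaves the catheter laboratory. Section 2.5.2 has all tracings reviewed blinded, with patient information anonymized.

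**The concern.** To learn whether a device shortens time to reperfusion, the device must be able to act before the treatment decision in at least some patients, and their times must be set against those of patients managed without it. Here the decision precedes the device in every STEMI patient, and there is no second pathway to compare with.

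As written, the study therefore commits itself to a result that it cannot produce. Either the aim goes unanswered, or an agreement or accuracy result is taken to stand in for a time benefit. Section 4 leaves the second route open, because its inference to reduced time rests on diagnostic capability and nothing else. Readers could act on a claim of earlier reperfusion, so the wording matters even though the primary analysis is sound.

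**Working it through.** This is a question of design logic. The article gives no time estimate to recompute, so the check compares the aim with each element it would need.

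**1. Does the handheld come before the diagnosis?** No. Section 2.3 makes a 12-lead diagnosis part of the definition of the STEMI group. Section 2.5.1 describes the order (12-lead ECG in the emergency room, then the catheter laboratory) as what generally happens, which alone would allow exceptions. The entry definition in section 2.3 does not.

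**2. Does it come before the decision to treat?** No. The recording is part of preparing a procedure already decided on. Under the fallback it may even follow reperfusion.

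**3. Does the reading inform care?** Nothing says so. Blinded review of anonymized tracings points the other way. This is an inference from timing and blinding, not an explicit statement.

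**4. Is there a comparison?** No. The study is observational, and no patients are managed on the handheld. The group without STEMI comes to angiography through an outpatient clinic and has no STEMI reperfusion time to shorten.

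**5. How many patients could inform the time aim?**

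- Planned STEMI patients (section 2.6): 72.
- Expected inferior wall STEMI at the assumed 40%: 0.40 × 72 = 28.8, about 29. After the 10% dropout allowance: 0.90 × 28.8 = 25.9, about 26.
- Patients in whom the handheld precedes the diagnosis: 0, whichever denominator is used.

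The zero restates the design; it is not an estimated effect.

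**6. Does the sample size serve the time aim?** The stated total of 216 can be approximately reproduced from kappa alone. Take p = 0.13, κ0 = 0.8, κ1 = 0.98, two-sided α = 0.05 and power 80%, with the goodness-of-fit method for a binary kappa. The article does not name its method, so this choice is an assumption.

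- n = (1.960 + 0.842)² / S, where S is the sum over the three outcome cells (both positive, discordant, both negative) of (difference in cell probability)² / (cell probability under κ0).
- p(1 − p) = 0.1131, and 0.1131 × 0.18 = 0.02036.
- S = 0.02036²/0.10738 + (2 × 0.02036)²/0.04524 + 0.02036²/0.84738 = 0.00386 + 0.03664 + 0.00049 = 0.04099.
- n = 7.849/0.04099 = 191.5, rounded up to 192.
- 192/0.9 = 213.3, rounded up to 214. The next multiple of 3, for the 1:2 ratio, is 216.

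No input concerns time. The figure supports the agreement aim and is silent on the other.

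**7. Does accuracy imply a time reduction?** No. Agreement between two recordings made one after the other shows whether the second would have given the same diagnosis. It does not show how long the handheld takes to deploy and read at first contact, or whether treatment would start sooner.

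**The case against.** The best defence is that the time statement is motivation rather than an objective. Section 2.2 names only sensitivity and specificity, and sections 2.1, 2.6 and 2.7 agree with it. The Introduction's sentence can be read as giving the reason for studying agreement. Elsewhere the article hedges: the Introduction, the Discussion and the limitations speak of potential or expected gains, the abstract's conclusion speaks of feasibility, and section 4 is conditional. This stands in part. It shows that the primary objective is untouched and limits the weight of the point. It does not dispose of the abstract, where the time statement is added after the accuracy aim as something the study will determine. Nor does the condition in section 4 help, since capability to diagnose does not entail a shorter time.

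A second defence is that a journal article condenses, and that a time endpoint may be defined in the full protocol or analysis plan. That is fair as far as it goes, and the absence of a time endpoint or clock definition here is not counted as a defect. But no such endpoint could repair the aim, because the obstacle is patient selection and the order of recordings, both fixed in this document.

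Three stronger readings should be resisted.

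- A reader might subtract the 30 s recording from the 3 to 5 min quoted for a 12-lead ECG and call 2.5 to 4.5 min the largest possible gain. The Introduction also describes that 3 to 5 min as a minimum, and handheld set-up and reading are not counted, so the difference bounds the gain in neither direction.
- A reader might conclude that the investigators will report accuracy as a time benefit. That would be a prediction; the document promises no such analysis.
- A reader might infer that the accuracy objective is undermined. Nothing in this point supports that.

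**Conclusion.** The point holds in limited form. The abstract and Introduction state a time-reduction aim that no result of this study can answer, and section 4 draws a time conclusion from diagnostic capability alone. The size is categorical: none of the 72 planned STEMI patients can contribute evidence on time to reperfusion.

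This rests on the entry definition in section 2.3 and the recording order in section 2.5.1 being followed as written. It would change only if some patients had the handheld recorded at first contact, before the 12-lead ECG, with a comparator. What needs correcting is a secondary aim and the conclusion; the primary objective, the 216 and the accuracy analysis stand.

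**What to change.** Four wording changes:

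1. **Abstract, Background:** state the purpose as assessing how well the handheld identifies inferior wall STEMI, not its utility for shortening time to diagnosis.
2. **Abstract, Methods and Design, and the last paragraph of the Introduction:** remove the undertaking to determine an effect on time to reperfusion. Limit the aim to agreement, sensitivity and specificity against the 12-lead ECG for inferior wall STEMI.
3. **Introduction and Discussion:** keep time saving as rationale, labelled as a hypothesis for a later study in which the device is used before the diagnosis and compared with usual practice.
4. **Section 4:** say that adequate accuracy would justify such a study, and that this study does not measure time to diagnosis or treatment.

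Adding a comparison of acquisition times is not recommended as a substitute. The handheld is set up in procedure preparation and the 12-lead ECG in the emergency room, so the settings differ, and the article does not say that a 12-lead acquisition time is logged.

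The cost is a narrower claim. No new data, patients or analyses are needed, and the change can be made whatever the stage of enrolment.

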## 1. Introduction

ST-T segment elevation myocardial infarction (STEMI) is a critical condition that requires rapid diagnosis and treatment [1]. The European Society of Cardiology 2017 guideline and the American Heart Association guideline suggest time targets related to the diagnosis and treatment of STEMI [2,3]. The usual practice is to diagnose STEMI in patients with chest discomfort or other ischemic symptoms and new ST-segment elevations in two contiguous leads [4]. Electrocardiography (ECG) should be performed within 10 min of the first medical contact, and if STEMI is diagnosed, percutaneous coronary intervention (PCI) should be performed within 60 min (wire crossing) at a primary PCI center [2,3]. However, when obtaining a 12-lead ECG from a patient complaining of chest pain in the emergency room, owing to the large size of the machine, it takes 3–5 min to move it next to the patient and record the ECG.

Recently, various ECG monitoring devices have been developed to diagnose arrhythmia such as atrial fibrillation through long-term monitoring [5,6]. Several studies have attempted to obtain chest lead equivalents or diagnose STEMI using a single-lead handheld ECG recorder or a smartwatch and determine its correlation with a standard 12-lead ECG [7,8,9,10]. Moreover, the recent research focus has been to generate a 12-lead ECG from a single-lead ECG [11] or to predict STEMI using artificial intelligence [12]. However, studies related to diagnosis using a handheld 6-lead ECG have not yet been published.

The smartphone-based handheld 6-lead ECG recording device, Alivecor Kardia Mobile 6 L, has two front transducers and a back transducer. It contacts both the upper limbs and one lower limb (e.g., left iliac crest, thigh, knee, and lower abdomen) to obtain all limb leads (I, II, III, aVR, aVL, and aVF). Anterior wall or lateral wall STEMI generally requires a precordial lead ECG in addition to a limb lead ECG for diagnosis [4]. Inferior wall STEMI can be diagnosed using limb leads alone. The capability to diagnose inferior wall STEMI by recording an ECG for 30 s using a handheld ECG device could potentially expedite diagnosis compared to existing devices that require significant time to move or attach to a standard 12-lead ECG device (at least 3 to 5 min). The use of this handheld device is expected to shorten the time required for diagnosis and making treatment decisions for inferior wall STEMI.

This study aims to evaluate the level of agreement between the results of a handheld 6-lead ECG device and a standard 12-lead ECG in the diagnosis of inferior wall STEMI to determine whether the use of the handheld device can reduce the time needed for reperfusion treatment through faster diagnosis.

## 2. Materials and Methods

### 2.1. Study Design

Handheld 6-lead ECG device for the early detection of acute inferior wall ST-T segment elevation myocardial infarction (HINT-MI) is an investigator-derived, multicenter, observational prospective study to evaluate the ability of a handheld 6-lead ECG device to diagnose acute inferior wall STEMI (reg. no. clinicaltrials.gov NCT05777083). By comparing a 6-lead ECG using a handheld device and a 12-lead standard ECG in patients with various types of STEMI and those without STEMI, the diagnostic accuracy of the 6-lead handheld ECG device in inferior wall STEMI will be evaluated.

### 2.2. Primary Objectives

This study will investigate the sensitivity and specificity of a handheld six-lead ECG device compared to a 12-lead ECG for the diagnosis of acute inferior wall myocardial infarction.

### 2.3. Study Population

Two primary PCI centers in South Korea are participating in this study, representing full coverage of all levels of care, including state-of-the-art tests, monitoring, imaging equipment, the latest treatment regimens, access to specialists, and intensive care units. The study subjects will consist of two types of patients: (a) patients who will first visit the emergency room and be diagnosed with various types of STEMI by a 12-lead ECG and undergo primary PCI, and (b) patients without STEMI who will undergo coronary angiography for chest pain after visiting an outpatient clinic. All the patients enrolled in this study will provide their voluntary informed consent.

In the case of patients with all kinds of STEMI, a surface 12-lead ECG in the emergency room and coronary angiography results will be used to screen for STEMI. Patients initially diagnosed with STEMI by ECG but later confirmed not to have a myocardial infarction by additional tests (coronary angiography and serum cardiac markers) will be excluded from the study. The diagnosis of myocardial infarction will follow the criteria of the fourth universal definition of myocardial infarction [4]. Patients with severe complications of myocardial infarction such as cardiogenic shock, respiratory failure, or decreased consciousness will be also excluded.

### 2.4. Six-Lead Handheld ECG Recorder

A recently developed wearable device for the detection of arrhythmia, a handheld 6-lead ECG recorder based on a smartphone (Kardia Mobile 6 L TM; Alivecor Inc., San Francisco, CA, USA), enables the patient to measure and transmit the ECG of the limb leads (Figure 1). It has been clinically validated for detecting atrial fibrillation in various populations. In our study, a handheld 6-lead ECG recorder will be used to record the limb leads. Access to the data is restricted to those authorized by institutional review board to handle data related to patient care and this study. The server to which the ECG is transmitted will be managed by the manufacturer. The device manufacturers had no role in the trial design, data accrual, or analysis.

### 2.5. ECG Recording

#### 2.5.1. Patients with STEMI

Among all patients with various types of STEMI who visit the emergency room and do not meet the exclusion criteria, an ECG using a 6-lead handheld device will be recorded, in addition to a basic 6-lead ECG monitor and a 12-lead ECG. In general, all patients with STEMI who visit the emergency room undergo a 12-lead ECG in the emergency room and then move to a catheterization laboratory for coronary angiography. In this study, the first 6-lead ECG by the handheld device will be recorded for 30 s in the supine position. To prevent any treatment delays, we will record the handheld ECG as part of the procedure preparation process, including the attachment of basic monitoring. If the first handheld recording is not available, it will be recorded before leaving the catheter lab.

During the procedure, a wired 6-lead ECG is typically attached to continuously monitor the patient’s condition. We will record this data for 30 s before and after the procedure. Finally, a 12-lead ECG will be recorded within 1 h after moving to the intensive care unit or emergency room, according to the general myocardial infarction treatment plan.

#### 2.5.2. Subjects Receiving CAG without STEMI

Data will be collected from patients who do not meet the exclusion criteria among those without STEMI who visit the hospital for chest pain and are hospitalized to undergo coronary angiography. In general, for patients admitted to the hospital for coronary angiography via an outpatient clinic, a standard 12-lead ECG is performed in the ward. While preparing for the procedure, basic monitoring (such as 6-lead ECG or pulse oximetry) will be performed immediately upon arrival of the patient in the angiography room, and a handheld 6-lead ECG will be recorded for 30 s in the supine and sitting position, before or after the procedure. At the same time, the data from the wired 6-lead ECG continuously monitoring the patient will be stored and collected (Figure 2).

A standard 12-lead ECG, 6-lead ECG monitor recording, and handheld 6-lead ECG data will be reviewed in a blinded manner by cardiologists with anonymized patient information. The ECG results will be matched with the case number and the sensitivity and specificity of the handheld 6-lead ECG performed before the procedure will be compared to the standard 12-lead ECG employed for the diagnosis of inferior wall myocardial infarction. The diagnostic criteria of inferior wall myocardial infarction in the ECG will be considered as new ST-elevation at the J-point in 2 leads among II, III, aVF leads, with the cut-point of ≥1 mm (Figure 3). The resting ECG results of each method will also be compared. Wired 6-lead monitor recordings will be further used to verify the handheld 6-lead ECG recordings.

### 2.6. Sample Size Estimates

Based on the diagnosis of inferior wall myocardial infarction using a standard 12-lead ECG, it was assumed that >98% of inferior wall myocardial infarctions can be diagnosed using a handheld 6-lead ECG. Based on the existing literature, we assumed that the prevalence of inferior wall STEMI among all STEMI patients would be 40%, and subjects with STEMI and those without STEMI would be recruited at a 1:2 ratio [13]. To obtain the Cohen’s kappa coefficient, with minimum acceptable kappa (κ0): 0.8, expected kappa (κ1): 0.98, proportion of outcome (p): 0.4 × 1/3 = 0.13, significance level (α): 0.05 (two-tailed), power (1 − β): 80%, expected dropout rate: 10%, the target number of subjects was deemed to be 216 in total (72 subjects with STEMI and 144 subjects without STEMI).

